## Randomisation

After completion of baseline assessments, participants will be individually randomised using minimisation with a 1:1 allocation ratio. Randomisation will be undertaken centrally using MinimPy (an open source, minimisation programme for allocation of participants to groups in randomised trials) [42]. Randomisation will be stratified by cancer type (breast, prostate, or colorectal) and disease status (advanced/metastatic disease vs. not). After the first participant has been randomly allocated, each subsequent participant will be allocated to the trial arm with the lowest imbalance score, with the addition of a 20% random element to reduce predictability of outcomes. The imbalance score is calculated based on hypothetical allocation of the next participant to each arm [43].

A member of the research team not involved with recruitment or data collection will use MinimPy to generate the allocation sequence as each person is recruited into the study. Intervention participants will be informed about their allocation arm by letter, with an appointment time for their intervention telephone/video call. Control participants will be informed via telephone or email.

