## Feasibility outcomes

The feasibility and acceptability outcomes are described in detail in Table 1 and include the recruitment and retention rates as well as app usage and engagement. These outcomes will be used to assess whether a future definitive trial could continue as per the current protocol, or if revisions are required before moving to the larger trial. The results of a power calculation will be considered alongside the recruitment and retention rates in order to estimate the number of participants that would need to be invited to provide the required sample size, to assess if this is feasible. In addition, if study enrolment is less than 30% or the 3-month retention rate is less than 65% we will consider if the trial procedures need modifying to make them more acceptable. Adaptations will be made to the assessment measures if the results indicate that these were not acceptable to participants or that participants were unable to complete them online. If more than 50% of the intervention participants do not download or use the app, or we are not able to deliver the behaviour change techniques (BCTs) to them as planned then this will trigger discussion about acceptability of the intervention. In lieu of clear published guidelines to base these values on these are pragmatic decisions that will trigger discussion about adaptation of the protocol. As part of the economic evaluation, a value of information analysis will be conducted. Value of information analysis helps ascertain the likely value of obtaining further information and therefore may provide useful information in the context of proceeding to a full RCT. While the listed criteria will be the primary criteria considered we will also examine the results from all data collected and any issue relating to successful trial delivery will inform decisions about progressing to a larger trial.

**Table 1 Tab1:** Feasibility and acceptability outcomes

Outcome	Measure
Recruitment rate	
Interest	Percentage of those potentially eligible (from medical records and clinician approval) who are interested and willing to answer further eligibility questions.
Enrolment	Percentage of participants who are interested and eligible who are randomised.
Acceptability of randomisation	The percentage of participants who withdraw upon being informed of allocation (within 1 week of randomisation). The percentage of potential participants who state that randomisation is their reason for declining to participate.

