Feasibility of administering the intervention	The percentage of the intervention group who: - receive a behavioural support call. - self-report successfully downloading the app.
Acceptability of the intervention	Percentage of participants who report that no aspect of the intervention (leaflet, call, planner, app) was useful. Percentage of withdrawals from intervention group compared to control group. Percentage of reasons for withdrawal relating to the intervention.
Retention rate	The percentage of participants, in each group, who complete any of the T1 follow-up assessment measures.
Acceptability of outcome assessments	The percentage of participants who consent who complete any baseline assessments. Completion rates, in each group, for each of the assessments at: - baseline - follow-up
Willingness of participants to consent to linkage with HES/NCRAS registries for long-term follow-up	The percentage of participants who consent for this aspect of the study.
Acceptability of online assessments	The percentage of participants who require help from a researcher to complete questionnaires. The percentage of potential participants who give this method of data collection as a reason for declining to participate.
Acceptability of providing informed consent online	The percentage of potential participants that state that they are unable/unwilling to provide consent online.
Self-reported app usage and engagement	Percentage of participants in the intervention group who report using the app for less than a month.
The proportion of screened participants ineligible and reasons for ineligibility	The number of participants screened and deemed ineligible for each inclusion/exclusion criteria.
Potential sociodemographic biases in recruitment	Anonymised aggregate socio-demographics (age, gender, ethnicity, Index of Multiple Deprivation, cancer type, cancer stage, time since diagnosis, treatment completed and started) of potentially eligible participants (from medical records and clinician approval) who did not participate in the trial compared with the study sample characteristics.
Fidelity of intervention delivery in the telephone/video calls	Average percentage of required behaviour change techniques covered in 25% of participants’ intervention calls (randomly selected) scored against a checklist.

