## Measures

Measurement timepoints for the pilot are baseline (T0) and 3 months (T1; operationalised as 12–16 weeks from randomisation). When a participant provides consent they will be sent URL links to online questionnaires via email (with the option to complete these by phone with a researcher if they experience difficulties), and mailed weighing scales (Seca 803 if they weigh less than 150kg and Seca 813 if they weigh over 150kg), a tape measure (Seca 201), and an activPAL4micro accelerometer (PAL Technologies Ltd., Glasgow, UK).

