### Physical activity (T0 and T1)

Physical activity will be measured using thigh-worn activPAL4micro accelerometers that participants will be asked to wear continuously for seven days (PAL Technologies Ltd., Glasgow, UK). The activPAL protocol, which follows published recommendations for using the device and expert advice from the Trial Steering Committee, includes waterproofing the device using specially designed nitrile sleeves and waterproof dressings, asking participants to wear it continuously, and including the data for analysis if 3 days of data are available [61]. Participants will be mailed instructions on how to wear the device, a log-sheet to record when the device was worn and bedtimes and waketimes, and a freepost envelope to return it. The primary outcome of the future full RCT will be activPAL-assessed average daily brisk walking (> 100 steps/min). The activPAL has shown excellent reliability and validity in measuring step number and cadence (steps/minute) and has been used in other studies with people LWBC and clinical populations [62, 63]. Other physical activity outcomes that will be explored are total daily steps, minutes of light physical activity, standing time and sitting time.

Participants will also complete the Godin Leisure-Time Exercise Questionnaire (GLTEQ) [64], which has demonstrated favourable validity and reliability against objective measures of physical activity and is widely used in oncology research [64, 65]. The questionnaire will be adapted to add a question about duration of activities to allow calculation of minutes of MVPA, in addition to the leisure score index, a practice that is common in oncology research [65].

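### Completion of each baseline assessment is defined by randomised group, which leaves out consenters lost before randomisation and can overstate the acceptability of baseline measures

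*Protocol article*

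**What the plan says.** Four statements in the protocol article bear on this point.

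- **Order of events.** Measures: "When a participant provides consent they will be sent URL links to online questionnaires via email"; the scales, tape measure and activPAL are mailed at the same stage. Randomisation: "After completion of baseline assessments, participants will be individually randomised using minimisation with a 1:1 allocation ratio".
- **Per-instrument measure.** Table 1, acceptability of outcome assessments: "Completion rates, in each group, for each of the assessments at: - baseline - follow-up".
- **Other measures that touch the same people.** The same row has "The percentage of participants who consent who complete any baseline assessments". The enrolment row has "Percentage of participants who are interested and eligible who are randomised".
- **Use of the results.** Feasibility outcomes: "Adaptations will be made to the assessment measures if the results indicate that these were not acceptable to participants". No numerical threshold is attached to this. The section adds that "we will also examine the results from all data collected and any issue relating to successful trial delivery will inform decisions" about progression.

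The article does not say which baseline measures must be complete before a participant is randomised. Its only activPAL completeness rule, "including the data for analysis if 3 days of data are available", concerns inclusion in the analysis and not entry to randomisation.

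**The concern.** The instruments go out at consent, but a participant has a group only after randomisation. A baseline rate calculated by group therefore covers only those who got through baseline far enough to be randomised. Someone who consents, fills in a questionnaire, does not manage the activPAL and is not randomised counts as a success on the any-assessment measure and is absent from the activPAL rate.

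Feasibility and acceptability of procedures are the primary outcomes of this pilot. The activPAL asks for seven days of continuous thigh wear and supplies the intended primary outcome of the full trial, so a hidden loss would matter most for this instrument. If it deterred consenters before randomisation, the per-instrument baseline rates could look better than experience at the point of use. The trial team would then have weaker grounds for deciding which procedure to revise.

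The split by arm also adds nothing at baseline. Allocation has not yet happened when the measures are completed, so any difference between arms is chance.

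**Working it through.** The article states no completion rate or threshold for this outcome, so there is no figure to reproduce. The check compares denominators and then illustrates the possible size.

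**Step 1: who is counted in each measure**

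| Measure | Denominator | Shows which instrument failed? |
|---|---|---|
| Any baseline assessment completed | all consenters | no; detects only those who complete nothing |
| Completion of each assessment at baseline, by group | randomised participants | yes, but only among the randomised |
| Enrolment | interested and eligible | no; mixes baseline losses with people who did not consent |
| Completion of each assessment at follow-up, by group | randomised participants | yes, and properly defined |

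No row gives completion of each baseline instrument among the people to whom it was sent.

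**Step 2: inputs (all assumed; the article gives none)**

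Per 100 consenters:

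- q = number who complete nothing and are not randomised
- f = number who complete the questionnaires but fail the activPAL
- s = share of those f who are randomised anyway

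**Step 3: formulas**

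- Any-assessment rate = (100 − q) / 100
- activPAL completion among consenters = (100 − q − f) / 100
- activPAL completion in the randomised groups = (100 − q − f) / (100 − q − f + s·f)

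**Step 4: example with q = 5, f = 20**

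- Any-assessment rate = 95/100 = 95%
- Among consenters = 75/100 = 75%
- In-group, s = 0: 75/75 = 100%
- In-group, s = 0.5: 75/(75 + 10) = 75/85 = 88.2%
- In-group, s = 1: 75/(75 + 20) = 75/95 = 78.9%

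**Step 5: example with q = 0, f = 20**

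- Any-assessment rate = 100%; among consenters = 80%
- In-group = 80/80 = 100%, 80/90 = 88.9% and 80/100 = 80% for s = 0, 0.5 and 1

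In this second case the any-assessment measure reads 100% although one consenter in five fails the activPAL, so it cannot stand in for a per-instrument rate. With s = 1 the overstatement disappears, because nobody is lost before randomisation.

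**Step 6: range**

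For q of 0, 5 or 10 and f of 5, 10, 20 or 30, the in-group rate exceeds the rate among consenters by:

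- 5 to 40 percentage points at s = 0 (lowest at q = 0, f = 5: 100 − 95; highest at q = 10, f = 30: 100 − 60)
- 0 to 9.4 points at s = 1 (highest at q = 10, f = 5: 85/90 = 94.4% against 85%)

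The result depends mainly on s, and the article does not settle s.

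**The case against.** The strongest reply is that the article never says every measure must be complete before randomisation. Planning a baseline completion rate for each assessment by group makes sense mainly if some randomised people have measures missing. On that reading an activPAL failure stays in the denominator and is visible. This stands, and it limits the size of the problem. It does not remove the problem, because consenters lost before randomisation are still left out.

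A reader might go further than the documents allow in three ways.

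- **That the reported baseline rates will be close to 100%.** This follows only if every measure is a condition of randomisation. That is the literal reading of the Randomisation section, but the article does not confirm it.
- **That activPAL losses would show up only as lower enrolment.** People who complete nothing also lower the any-assessment measure. Follow-up completion of each assessment by group could show a burdensome device too. The interviews at the end of the trial explore experiences of participation. These give partial cover, though none is a per-instrument baseline rate among consenters.
- **That the decision to adapt the measures turns on this rate.** The article sets no threshold and undertakes to look at all data collected. A visible loss between consent and randomisation could be picked up that way, although the same sentence treats the listed criteria as the primary ones.

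It can also be said that exact denominators for descriptive outcomes belong in a fuller document. That would answer a complaint of missing detail. Here the article states a denominator, and it does not fit the article's own order of events.

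**Conclusion.** The point holds in a limited form. As defined, every per-instrument baseline completion rate is conditional on having been randomised, and randomisation follows baseline. The rate carries no information if all measures are required first, and it is incomplete if they are not. The two neighbouring measures recover part of the loss but cannot attribute it to an instrument.

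The direction is known: where consenters who fail an instrument are not randomised, its acceptability at baseline is overstated. The size is not known and may be zero. The 75% against 100%, 88% or 79% is an illustration that rests wholly on assumed losses and on the assumed share of partial completers randomised. Follow-up completion by group is unaffected. Because acceptability of procedures is a primary aim and the correction is small, the change should be made.

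**What to change.** In the Table 1 row on acceptability of outcome assessments:

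1. Report baseline completion of each assessment (questionnaires, weight and waist, valid activPAL data) pooled, with all consenting participants as the denominator.
2. Keep the existing measure of completing any baseline assessment beside it, since it identifies people lost before doing anything.
3. Use the split by group for follow-up only.

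In the Randomisation section, state which baseline measures must be complete before a participant is randomised and how partial completers are handled.

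The cost is a changed denominator in one row and one added sentence. Returns of the activPAL need to be logged for consenters who are not randomised as well; the devices come back by post, so this should be confirmed and not assumed. The reported baseline completion may look less favourable.

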## Intervention

The intervention is described according to the template for intervention description and replication (TIDiER) checklist which is provided as Supplementary Material [44]. The intervention was designed with input from people affected by breast, prostate, and colorectal cancer throughout, including our background empirical research and several Patient and Public Involvement (PPI) activities [25, 29, 30].

The intervention involves the Active 10 app along with additional behavioural support (outlined in the subsequent sections).

The Active 10 app was developed by Public Health England and will be maintained by its successor bodies. It was selected for the current study because it contained a number of the features that people LWBC and clinicians highlighted as important and is developed and maintained by a UK health agency, sponsored by the UK Government [29, 30, 45]. Screenshots of the Active 10 app are presented in Fig. 3. The app encourages users to walk briskly for 10 min (known as one ‘Active 10’) and users can set a goal to complete between 1 and 3 Active 10s per day, with the ultimate aim of reaching 30 min of at least moderate-intensity physical activity per day. Each minute of brisk walking counts towards the Active 10 goals, to reflect the recent change in the UK physical activity guidelines removing the guidance that bouts of at least 10 min were required [46]. The app distinguishes between total walking and brisk walking. Brisk walking confers greater health benefit than slower paced walking and is captured by Active 10 when participants walk at a rate of approximately 100 steps per minute or more [47].

**Fig. 3 Fig3:**
[figure not shown]
Screenshots of Active 10 app

Participants will be mailed a pack that contains a leaflet recommending the use of/describing how to download the Active 10 app as well as information about the importance of physical activity after cancer. The pack will also contain walking planners designed to support action planning and self-monitoring of walking plans. These materials will be accompanied by a letter from the participant’s clinical care team endorsing physical activity and using Active 10. Participants will also receive additional behaviour change support from the research team via two telephone/video calls, one shortly after randomisation and a second after 4 weeks. During the initial call researchers will discuss the recommended physical activity guidelines for people LWBC, the associated benefits of meeting these guidelines and of increasing physical activity by any amount; work through the concept of habit formation and using the walking planner; help with setting daily walking goals; help with developing a plan/habit for opening the app; and help with downloading the app for participants who have not already done so. During the second call, researchers will check if participants are using the app and increasing their brisk walking; remind them of their goals; and recap any of the information from the first call. These calls are intended to closely replicate conversations that a health care professional could have with a patient as part of routine care, should this intervention be implemented on a larger scale.

### Theoretical basis of the intervention

Active 10 is a publicly available app and was not developed specifically for this study. Therefore, the app content was independently coded according to the Behaviour Change Technique Taxonomy (BCTTv1) (PL, NM), any discrepancies were discussed before agreement was reached on the techniques used [48]. Table 2 outlines the intervention components across the five elements of the intervention and the relevant coded BCTs [48]. The central feature of the Active 10 app is that it allows participants to monitor their activity. Self-monitoring of physical activity using a variety of technologies has been shown to successfully promote increases in physical activity in the general population and among people LWBC [49, 50]. The intervention content provided in addition to the Active 10 app was informed by habit theory and includes BCTs that have shown efficacy in promoting physical activity in inactive adults, have been associated with improved adherence to physical activity interventions in people LWBC, and that were practical to use in the context of providing brief written materials and behavioural support [28, 51–54].

**Table 2 Tab2:** Intervention components and the behaviour change techniques

	Intervention component	Behaviour change techniques (BCTTv1)
Active 10 App	Introducing the app into participants’ environment	12.5
	The App is hosted by Public Health England	9.1
	Introduction: “Brisk walking is…” “Every minute counts” “Aim for 10 min or more a day”	4.1
	I’m doing Active 10 because…	N/A
	Set your targets (1, 2, or 3 Active 10s a day)	1.1
	Walking tracker (minutes of walking and minutes of brisk walking)	2.2
	Rewards	10.3, 10.6
	Links to useful websites (e.g. NHS)	N/A
	Link to a discussion group for the app	3.1
	Articles on starting small and building up, physical and mental health benefits, disabilities, how much physical activity to do, and a link to a running app	5.1, 5.6
	Ability to set reminders	7.1
	Tips: social distancing, set a reminder, keep track (use app to see how you’re doing), plan ahead (the day before or in the morning).	N/A
Leaflet and accompanying letter from clinical team	Clinical team recommendation to read and use the information provided and to download Active 10	6.3, 9.1
	Branding: Yorkshire Cancer Research, UCL, University of Leeds, University of Sheffield, Doncaster and Bassetlaw Teaching Hospitals	9.1
	Physical activity improves side effects of cancer treatment, recovery and risk of recurrence, mood and confidence. Physical activity reduces risks of other health problems.	5.1, 5.6
	Quotes from cancer patients: used physical activity to cope with fatigue, chose walking to try to meet guidelines	6.3
	People who have or have had cancer recommended to try to meet same physical activity guidelines as other adults. Brisk walking 2-3 times every day will meet the activity guidelines (150 min), the more the better.	9.1
	Recommends brisk walking. This should make you breathe a bit faster…	4.1
	Recommends start small then build up	N/A
	Information on downloading Active 10	N/A
	Recommends planning	N/A
	Recommends walking at the same time or in the same situation	8.1, 8.3
	Recommends tracking behaviour using the walking planners and Active 10	N/A
	Links to resources about the health benefits of PA	5.1, 5.6
	Links to resources to support walking	6.3
Walking planner	Adding planner to people’s environment	12.5
	Promotes habit formation	8.1, 8.3
	How many Active 10s are you aiming for	1.1
	Plan: when, where, for	1.4, 7.1
	Did you complete plans?	2.3
	Did you meet your target?	2.3
	How did you feel after you walked briskly?	5.4
	Reminder not to worry if miss a day and to adjust goals as required (reduce if finding it hard and increase if meeting goals and feel able).	N/A
Intervention: Phone/video call 1	Introduce self as working with clinical team at the hospital	9.1
	Ask participants how their cancer and treatment has impacted their lifestyle and activity levels	N/A
	Discuss physical and mental health benefits of physical activity	5.1, 5.6
	Discuss motivations to increase activity	9.2
	Discuss concerns about increasing activity	9.2
	Help participant to work out ways to overcome concerns about brisk walking, provide information as appropriate	1.2
	Discuss why recommending brisk walking, including cancer patients have recommended this	6.3
	Describe brisk walking	4.1
	Provide information on government guidelines (150 min MVPA) as well as WHO Every Move Counts.	9.1
	Highlight building up over time	N/A
	Discuss how confident they are and how they can increase their confidence	1.2
	Suggest trying it to see if that increases their confidence	4.4
	If needed tell them that it is possible for them to do this and others have been able to	15.1
	Promote habit formation for initiating a walk	8.1, 8.3
	Make an action plan (when, what, how long)	1.4
	Promote self-reward during and/or after walking	10.7, 10.9
	Promote non-specific self-reward during and/or after walking	10.3, 10.6
	Promote using the app to track activity	2.2
	Promote specific cues	7.1
	Promote reminders	7.1
	Set a target number of Active 10s	1.1
	Promote asking friends to support, by encouraging and helping to remember to walk	3.2, 3.3
	Promote using the walking planner to track behaviour	2.3
	Encourage participants to use information provided to overcome their concerns about exercising	13.2
Intervention: Phone/video call 2	Remind them of their target	1.5
	Ask how they are getting on with their target	1.6
	Ask if they have or, if they want to change their target	1.5
	Ask participants what is preventing them from walking and what would help them to start (if relevant)	1.2
	Repeat any of the points from call 1 as appropriate	As above as relevant

1.1 Goal setting, 1.2 Problem solving, 1.4 Action planning, 1.5 Review behaviour goals, 1.6 Discrepancy between current behaviour and goal, 2.2 Feedback on behaviour, 2.3 Self-monitoring, 3.1 Social support (unspecified), 3.2 Social support (practical), 3.3 Social support (emotional), 4.1 Instruction on how to perform a behaviour, 4.4 Behavioural experiments, 5.1 Information about health consequences, 5.4 Monitoring of emotional consequences. 5.6 Information about emotional consequences, 6.3 Information about others’ approval, 7.1 Prompt/cue, 8.1 Behavioural Practice/Rehearsal, 8.3 Habit formation, 9.1 Credible source, 9.2 Pros and cons, 10.3 Non-specific reward, 10.6 Non-specific incentive, 10.7 Self-incentive, 10.9 Self-reward, 12.5 Adding objects to the environment, 13.2 Framing/Reframing, 15.1 Verbal persuasion about capability

Habit theory posits that habitual behaviours are performed when an impulse to act is automatically triggered in a particular situation by virtue of a mental association having formed between that situation and behaviour through repetition [27]. Habits predict behaviour particularly on days when people’s intentions are lower than usual and therefore support maintenance of behaviour, shielding it from temporary lapses in motivation [55]. In order to form a habit, a behaviour needs to be performed consistently in the same situation (termed context-dependent-repetition) [28]. It is possible to succinctly deliver this advice to participants, and interventions using this technique have shown positive changes in behaviour [56]. Distinction has been made between the habit of initiating a behaviour (i.e. an instigation habit) and that of performing it (i.e. an execution habit), and it is the instigation habit that predicts behaviour maintenance [57–59]. The advice given in the intervention leaflet and phone calls therefore recommend participants focus on forming instigation habits for doing physical activity, while gradually increasing the amount or intensity of activity they do on each occasion.

